#### Premature Withdrawal and Discontinuation Criteria

One of the limitations of dobutamine infusion is tachycardia. The infusion rate will be halved and/or discontinued if a patient develops tachycardia (heart rate ≥100 BPM) for more than 30 minutes despite adequate anesthesia/analgesia and fluid status (based on the aforementioned intervention). If the reduced dose does not correct the tachycardia, the infusion will be turned off. In addition, if at any point the attending staff raises concerns about the patient being at an increased risk because of study participation, the intervention will be stopped and the patient removed from the investigation. Moreover, if the patient decides they want to withdraw their consent at any point prior to publication, they will be excluded from the study and none of the information collected from them will be used for research purposes. The study intervention only applies during surgery and potentially for up to 4 hours postoperatively. All study participants will be fully monitored for the duration of the study intervention and beyond for up to 48 hours postoperatively. They will have immediate access to any additional care or intervention if required.

If patients are withdrawn from the study, we will continue to enroll consecutively until we have met our stipulated sample size of 20 patients per group. For patients who are withdrawn, we will seek permission to retain any data collected (especially demographic information) for comparison between those who were not and those who were withdrawn to determine whether they differ in any respect.

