#### Statistical Analysis

Data will be entered into REDCap (Research Electronic Data Capture; version 10.6.12; Vanderbilt University). Upon study completion, the data will be exported to SPSS software (version 29.0; IBM Corp) for analysis. Descriptive analyses, including mean, SD, median, and interquartile range for continuous data, as well as frequencies and percentages for categorical data, will be completed for all demographic and surgical characteristics and study outcomes. The underlying distributions of all continuous data will be assessed for normality using the Shapiro-Wilk test. Tissue oxygenation will be compared using independent sample *t* tests if the data are normally distributed and the Mann-Whitney *U* test in the event that they are not. Secondary outcomes will be compared between the 2 groups using the Fisher exact or Pearson chi-square tests (as appropriate depending on cell sizes) for categorical data and independent samples *t* tests (or the Mann-Whitney *U* test depending on the underlying distribution) for continuous data. Intent-to-treat analyses will not be conducted, and no adjustments will be made for missing data. Repeated measures analysis of variance (ANOVA), with the group as a factor, will be used to compare the tissue oxygenation over time (baseline, 1, 2, 4, and 8 hours postoperatively, along with baseline and postoperative day 1 and day 2 data). *P*<.05 will be used as the criteria for statistical significance, and no adjustment will be made for multiple comparisons. The possibility of a type I error will be acknowledged, and the actual *P* values will be presented for all comparisons.

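### Intention-to-treat is ruled out, no other analysis set is named, and patients removed after randomisation for study-related risk are replaced, so any removal breaks the randomised comparison

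*Protocol article*

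**What the plan says.** Four statements in the protocol article act together.

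- **Statistical Analysis:** "Intent-to-treat analyses will not be conducted, and no adjustments will be made for missing data". The statement is unqualified, and no per-protocol, as-treated or other set is defined in its place.
- **Premature Withdrawal and Discontinuation Criteria, removal:** if attending staff raise "concerns about the patient being at an increased risk because of study participation", then "the intervention will be stopped and the patient removed from the investigation".
- **Same section, replacement:** after a withdrawal, "we will continue to enroll consecutively until we have met our stipulated sample size of 20 patients per group". For those withdrawn, "we will seek permission to retain any data collected (especially demographic information) for comparison" with the patients who stayed in. No use in the outcome analysis is mentioned.
- **Study Design, Randomization, and Blinding:** envelopes are opened before induction by research staff, by the attending anesthesiologist, or both. Removals during surgery therefore follow randomisation, and the person caring for the patient may know the arm.

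Tachycardia is handled separately: "The infusion rate will be halved and/or discontinued if a patient develops tachycardia" that persists. The text does not say that such a patient leaves the trial. The Control Group section allows dobutamine in controls when clinically indicated.

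**The concern.** Randomisation protects the comparison only if patients are analysed in the groups to which they were assigned. Here the removal criterion is unequal between arms. According to the Rescue Medication and Risk Management section, the departures from standard care are dobutamine, fluid therapy guided by cardiac output, and noninvasive oximetry. Controls receive only the oximetry. Risk caused by taking part can therefore hardly arise in a control.

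A staff concern during surgery would plausibly reflect haemodynamic state, which the Background links to flap perfusion. Removing such patients and filling their places would leave a selected intervention arm beside an unselected control arm.

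A second gap follows from ruling out intention-to-treat without naming a set. Nothing fixes how to analyse a patient whose infusion was reduced or stopped, or a control who received dobutamine. Such patients could be dropped or reclassified after unblinding, and with 20 per arm a few such choices matter. The stated objective is to test a treatment algorithm, and reducing or stopping the infusion is part of that algorithm. Leaving those patients out would answer a different question.

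**Working it through.** **1. The plan's own sample size reproduces.** Inputs from the Sample Size section: difference 1.75 − 0.50 = 1.25 kPa, SD 1.0, α 0.05 (two-sided), power 80%.

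n per arm = 2 × (1.960 + 0.842)² × (1.0/1.25)² = 10.05, rounded up to 11. This is the stated figure; the t-based solution is 11.09. The sample size is not the problem.

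**2. Replacement is not needed for power.** t-test power at 1.25 kPa and SD 1.0:

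| Analysed per arm | Power |
|---|---|
| 20 v 20 | 97.1% |
| 20 v 18 | 96.3% |
| 20 v 16 | 95.2% |
| 16 v 16 | 92.8% |

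**3. Possible bias.** The documents give neither a removal rate nor its link to the outcome, so both are assumptions. Let a fraction f of intervention patients, those with the lowest tolerance, be removed and replaced. Let rho be the correlation between tolerance and flap oxygenation. There is no true effect, no control is removed, and 20 per arm are analysed. With z_f the f-quantile of the standard normal and φ its density:

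bias in SD units = rho × φ(z_f) / (1 − f)

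Example for f = 10%, rho = 0.5: 0.5 × 0.1755 / 0.90 = 0.10.

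| f | rho | Bias (SD) | False claims of benefit (nominal 2.5%) | Two-sided error (nominal 5%) |
|---|---|---|---|---|
| 0 | any | 0 | 2.5% | 5% |
| 5% | 0.3 | 0.03 | 3.2% | 5.2% |
| 5% | 0.5 | 0.05 | 3.6% | 5.3% |
| 10% | 0.3 | 0.06 | 3.8% | 5.4% |
| 10% | 0.5 | 0.10 | 4.9% | about 6% |
| 20% | 0.3 | 0.11 | 5.1% | 6.2% |
| 20% | 0.5 | 0.18 | 8.0% | 8.7% |

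The error rates come from 100,000 simulated trials per setting. With rho = 0 there is no bias at any f.

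**4. What can still happen in this trial.** To end with 20 retained, f = 10% means 20 × 0.10/0.90 = 2.2 removals, and f = 20% means 20 × 0.20/0.80 = 5. The Results section reports 34 completed and no safety withdrawals, which leaves 40 − 34 = 6 places, or about 3 in the intervention arm if the arms are balanced so far.

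Suppose the least tolerant of those three is removed and replaced. The expected minimum of three standard normals is −0.846, so bias = 0.846 × rho / 20. That is 0.01, 0.02 and 0.03 SD for rho 0.3, 0.5 and 0.7. In simulation, false claims of benefit are then 2.7%, 2.9% and about 3.0%, with two-sided error about 5%.

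**The case against.** The strongest reply is that the rule has done no harm so far. With no safety withdrawals among 34 completed participants, removal rates of 10% to 20% are unlikely by the end, and one late removal would barely move the error rate. This stands, and it limits the size of the point. It does not make the rule sound. The rule still governs the remaining places, and the missing analysis set affects everyone already treated.

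The direction of bias is also an assumption. No section ties a staff safety concern to a lower oximetry reading, and bias could be absent or run the other way. That stands too: a shift toward the intervention is plausible, not shown.

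Three stronger readings are tempting, but the document does not support them:

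- **Tachycardia as a removal trigger.** A reader might infer that the intervention arm becomes those who tolerated dobutamine. The text only reduces or stops the infusion. Removal is a separate rule for staff concern.
- **Predictable late allocations.** A reader might infer that filling each group to 20 reveals the last assignments. The article describes concealed envelopes. It does not say how replacements are allocated or that recruiters see running counts.
- **Consent withdrawal as part of the same bias.** Excluding patients who withdraw consent is the patient's choice, is open to both arms, and is not related to the intervention in the same way.

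Nor can the unseen analysis plan or the condensed article format excuse the rule. Ruling out intention-to-treat is an explicit decision, not an omitted detail.

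**Conclusion.** The point holds in conditional form. The plan expressly rejects intention-to-treat, puts no defined set in its place, and allows replacement of patients removed for a reason that arises almost only in one arm. If any such removal occurs, the groups compared are not the groups randomised, and the estimate can be biased, plausibly toward the intervention.

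Under the assumed 10% removal and correlation of 0.5, the shift is about 0.10 SD. Measured against the protocol's own two-sided criterion, the inflation is modest. The record to date suggests a smaller effect still, and none from removals if none occur. It would be wrong to say that the comparison has already lost its randomised basis. What remains regardless is freedom after unblinding to decide who counts, in a trial of 40 whose result is meant to justify a larger one.

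**What to change.** Before unblinding, change the wording in two sections.

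- **Statistical Analysis:** the primary analysis includes all randomised patients in the group assigned. It uses every available 45-minute reading, whether or not the study intervention was reduced or stopped and whether or not a control received dobutamine. Keep a per-protocol comparison, with its set defined in advance, as a sensitivity analysis.
- **Premature Withdrawal and Discontinuation Criteria:** where staff raise a concern, state that the study intervention is stopped while oximetry readings and 30-day follow-up continue, unless consent is withdrawn. The clinical decision to stop is untouched. Do not replace randomised patients in the primary analysis.

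The cost is an amendment and slight dilution of the effect if some patients stop early. No extra patients are needed.

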**Figure 2 figure2:**
[figure not shown]
Depiction of the Holm perfusion zones [21]. Zone I is well recognized for being the most richly perfused as it contains the perforator vessels. The use of this zone during deep inferior epigastric perforator (DIEP) flap breast reconstruction surgery may provide optimal tissue flap perfusion.

Our secondary outcomes include (1) tissue oxygenation at baseline (preoperatively), intra-operatively and 1, 2, 4, 8 hours postoperatively, as well as the morning of postoperative days 1 and 2; (2) the amount of intravenous fluids (crystalloids, colloids, blood products) and vasopressors (eg, phenylephrine, ephedrine, norepinephrine, etc) administered intraoperatively and up to 4 hours postoperatively; (3) the need for intraoperative surgical vascular reintervention (ie, reanastomosis); (4) laboratory measures including perioperative pH, serum lactate, and hemoglobin measures; (5) incidence of postoperative nausea and vomiting; (6) hospital length of stay; (7) any postoperative complications including infection, hematoma, and those resulting from flap malperfusion (ie, partial/total flap loss and fat necrosis); (8) the need for postoperative intervention for flap-related issues; (9) overall patient satisfaction; and (10) days alive and out of hospital, all up until 30 days postoperatively.

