#### Approved Protocol

A tissue oximeter device (SnapshotNIR; Kent Imaging) will be used for all patients. This is a portable noninvasive monitor that measures tissue oxygen saturation using NIRS technology with the capability of saving images to allow for subsequent analyses. Measurements will be taken by holding the monitor at a standardized (30 cm) distance from the skin area where the oxygen levels are to be measured. Upon admission to the OR, preoperative baseline measurements (with patients breathing ambient air without supplemental oxygen) will be recorded over the abdominal flap tissue, followed by recordings immediately postinduction, 1-hour postinduction, when the abdominal flap is free (and still perfused by the chosen perforator arteries), before clamp removal postarterial reanastomosis, and 45 minutes following reanastomosis. All research personnel dedicated to this study will receive prestudy training on the perfusion zones and study outcomes to ensure that oxygenation measures are consistently taken from the same surgical region in relation to the perfusion zones (as described in Figure 2) throughout each case. In addition, the surgical team, led by authors [name], will assist with guiding the intraoperative oxygenation measurements with respect to flap location. However, the surgical team and attending anesthesiologist will be blinded to the Kent oxygenation measurements throughout the perioperative period, and surgery will be guided as per the standard of care. The ischemic period during which the flap is transferred (reflected by a fall in the oxygen saturation of the flap [23]) as well as the time of flap revascularization (characterized by increased oxygen saturation [23]) will be recorded. Upon completion of the surgical procedure, another NIRS-based monitor (Somanetics INVOS 5100C Cerebral/Somatic Oximeter; Medtronic) may be applied to the freshly reconstructed graft at the surgeon’s discretion. If deemed appropriate, a sticker will be applied over the flap for continuous graft oxygenation monitoring up to 48 hours postoperatively. However, if the surgeon requires the entirety of the graft to be exposed for visual monitoring (as per the standard care), a sticker/sensor will not be applied. Nevertheless, postoperative measures will be routinely recorded at 1, 2, 4, and 8 hours postoperatively, as well as on the morning of postoperative days 1 and 2 using the Kent device. All measures will be consistently taken at the same location [24]. Note that continuous intraoperative monitoring with the Somanetics INVOS Oximeter is not possible, as the sensors cannot be sterilized.

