
#### Intervention Group

The intervention will commence from the induction of general anesthesia and continue until 4 hours after surgery. Ringer lactate (2 ml/kg/h) will be commenced upon admission to the OR to satisfy maintenance fluid requirements. CO and stroke volume index (SVI) will be measured by one of 2 CO monitors: (1) FloTrac system (Edwards Lifesciences Corp), which attaches to the arterial line already in place in this surgical population; or (2) Starling SV system (Cheetah Medical), a noninvasive CO monitor that utilizes 4 stickers placed on the patient’s trunk. No more than 500 ml of intravenous fluid will be administered at anesthesia induction. In addition to the maintenance fluid described previously, patients will receive 250 ml fluid challenges with crystalloid as required until they are no longer fluid-responsive. Albumin 5% will also be allowed for fluid challenges at the discretion of the attending anesthesiologist. The absence of fluid responsiveness will be defined as the absence of a sustained rise in SVI of at least 10% for 20 minutes or more, at which point the patient will be considered fluid-optimized. At this point, a low-dose dobutamine infusion at a fixed rate (2.5 μg/kg/min) will be commenced and maintained until 4 hours postoperatively. The infusion rate will be halved and/or discontinued if the patient develops tachycardia (heart rate ≥100 BPM) for more than 30 minutes despite adequate anesthesia/analgesia and fluid status (based on the aforementioned intervention). Further fluid challenges will be performed by the attending anesthesiologist with the aim of maintaining maximal SVI throughout the case. Postoperatively, the patient will remain in the postanesthetic care unit (PACU) for a minimum of 4 hours (as per the current standard of care), after which the CO monitoring and the dobutamine infusion will be discontinued and the patient transferred to a level 2 step-down critical care unit. Ringer lactate at 2 ml/kg/h will be infused to satisfy maintenance fluid requirements until oral fluid intake is permitted by the surgical team, at which point the maintenance infusion will be stopped. Data collection and follow-up for such patients will be performed as per the standard of care.

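### The repeated-measures ANOVA enters baseline as an outcome level, omits the intraoperative readings, names no tested term and allows no handling of missing data; a baseline-adjusted mixed model would serve secondary outcome 1 better

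*Protocol article*

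**What the plan says.** Under Statistical Analysis, the protocol article plans: "Repeated measures analysis of variance (ANOVA), with the group as a factor, will be used to compare the tissue oxygenation over time". The time levels follow in brackets: "baseline, 1, 2, 4, and 8 hours postoperatively, along with baseline and postoperative day 1 and day 2 data". The section adds that "no adjustments will be made for missing data". It does not say whether the group main effect or the group-by-time interaction is the test.

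Under Objectives and Outcome Measures, the first secondary outcome is wider than that list: "tissue oxygenation at baseline (preoperatively), intra-operatively and 1, 2, 4, 8 hours postoperatively, as well as the morning of postoperative days 1 and 2". The Approved Protocol section schedules five intraoperative readings: just after induction, one hour after induction, with the flap free, and then "before clamp removal postarterial reanastomosis, and 45 minutes following reanastomosis". The same section places baseline before treatment: "preoperative baseline measurements (with patients breathing ambient air without supplemental oxygen) will be recorded over the abdominal flap tissue".

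The Intervention Group section starts the intervention at induction and ends it 4 hours after surgery, "after which the CO monitoring and the dobutamine infusion will be discontinued".

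**The concern.** Randomised groups can differ at baseline only by chance. As an outcome level, baseline adds a time point with no treatment effect to the group main effect; as a covariate, it would remove between-patient variance.

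The 1, 2 and 4 hour readings fall within the intervention window or at its end, and the 8 hour, day 1 and day 2 readings fall after it. With no tested term and no contrast fixed, the result depends on which line of the output is read. The plan also makes no multiplicity adjustment. The two readable terms behave very differently depending on whether the effect ends with the infusion or persists.

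Baseline is listed twice, so the text allows one 7-level model or two models (baseline with 1, 2, 4 and 8 hours; baseline with days 1 and 2). Neither has an intraoperative level, although much of the intervention is given in theatre.

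A classical repeated-measures ANOVA also needs complete rows. With 40 patients, a few scattered gaps could shrink the analysed set noticeably.

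**Working it through.** **Figure in the document.** The article gives no figure for the ANOVA. Its sample size figure reproduces: 2 × ((1.960 + 0.842) / 1.25)² = 10.05, rounded up to 11 per arm (difference 1.75 − 0.50 = 1.25 kPa, SD 1.0, two-sided 0.05, 80% power). This point does not affect it.

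**Inputs.** From the article: 20 per arm, the time levels, and the end of the intervention at 4 hours. Assumed, because the article gives no value: effect 0.9 SD (about what 20 per arm detects with 80% power at a single time point, 0.91 SD); equal correlation ρ of 0.3 to 0.7 between readings; independent gaps at 2%, 5% or 10% per reading.

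**Share of the effect kept by the group main effect** (mean of the effect over the levels):

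| Model | Effect at all postoperative readings | Effect at 1, 2, 4 h only |
|---|---|---|
| 7 levels | 6/7 = 86% | 3/7 = 43% |
| 5 levels (baseline, 1, 2, 4, 8 h) | 4/5 = 80% | 3/5 = 60% |
| 3 levels (baseline, days 1, 2) | 2/3 = 67% | no during-infusion reading |

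**Power, 7-level model, 20 per arm.**

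- Main effect: the variance of a patient mean is (1 + 6ρ)/7, and the noncentrality is 0.9 × share / √variance × √(20/2). For the infusion-only effect at ρ = 0.5: variance 4/7 = 0.571, shift 0.9 × 3/7 = 0.386, noncentrality 0.386 / 0.756 × 3.162 = 1.61, 38 df, power 35%.
- Interaction: λ = 10 × 0.81 × S / (1 − ρ), where S is the sum of squared deviations of the effect pattern from its mean. S = 3 − 9/7 = 1.714 for infusion-only and 6 − 36/7 = 0.857 for persistent. At ρ = 0.5, λ is 27.8 and 13.9 (F on 6 and 228 df).
- Baseline-adjusted mean of 1, 2 and 4 h: variance (1 + 2ρ)/3 − ρ². At ρ = 0.5 this is 0.417, noncentrality 0.9 / 0.645 × 3.162 = 4.41, 37 df, power 99%.

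| Effect | Term | ρ = 0.3 | ρ = 0.5 | ρ = 0.7 |
|---|---|---|---|---|
| Infusion-only | Group main effect | 47% | 35% | 28% |
| Infusion-only | Group-by-time | 93% | 99% | >99% |
| Infusion-only | Adjusted mean of 1, 2, 4 h | 99% | 99% | >99% |
| Persistent | Group main effect | 96% | 88% | 79% |
| Persistent | Group-by-time | 63% | 80% | 96% |

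In the 5-level model, main-effect power for the infusion-only effect is 71%, 57% and 48%.

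**Complete rows if deletion is listwise** (baseline always present). Six postoperative readings: 0.98⁶ = 89%, 0.95⁶ = 74%, 0.90⁶ = 53%, or about 35, 29 and 21 of 40 patients. Four readings (5-level model): 0.98⁴ = 92%, 0.95⁴ = 81%, 0.90⁴ = 66%.

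**The case against.** The strongest reply is that a comparison over time with group as a factor points at least as naturally to the group-by-time interaction. That term does not average during- and after-infusion readings; baseline serves there as the reference for change, and power for an infusion-only effect is high. This stands. A reader might infer that the plan does average the two periods, but that is true only of the main effect. What remains is that the term is not named, that the interaction is the weaker test for a persistent effect at lower correlations, and that it yields no estimate of either period's difference.

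Three further inferences go too far:

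- **That the intraoperative readings go unanalysed.** The t test or Mann-Whitney sentence in the same section is not limited to particular times, so it can cover them and every other single reading. The omission concerns the longitudinal model only.
- **That the plan deletes incomplete patients.** Row deletion is the usual result of this method combined with no adjustment for missing data, but it is not written.
- **That exposed flaps miss readings.** The Approved Protocol section says exposure only rules out the continuous sensor; the handheld readings are still taken routinely.

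Gaps may also be few: the article reports no loss to follow-up and high compliance. If they cluster within patients, more complete rows survive than shown. Finally, covariance structure and similar detail may be left to an analysis plan that is not shown. The method, its levels and the missing-data rule, however, are fixed here.

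**Conclusion.** The concern holds in a limited form. The text itself establishes that baseline is an outcome level and is listed twice, that no intraoperative level is included, that no tested term is named, and that missing data get no adjustment. The cost depends on the term read: the main effect keeps 43% to 86% of the true effect in a 7-level model, and power for the same 0.9 SD effect runs from 28% to over 99% across terms, effect patterns and correlations. These power figures rest on an assumed effect, equal correlation and, for the lowest values, no effect after 4 hours and a single 7-level model. The loss of patients is probable rather than stated, and its rates are illustrative.

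This is a secondary analysis that should be improved. It does not threaten the 45-minute primary comparison or the sample size.

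**What to change.** Replace the ANOVA with a linear mixed model of the post-baseline readings, with group, time, group-by-time and baseline oxygenation as a covariate, keeping every patient who has any post-baseline reading. Pre-specify two contrasts with 95% confidence intervals: the mean of 1, 2 and 4 hours (during the intervention) and the mean of 8 hours, day 1 and day 2 (after it). Either add the intraoperative readings to the model or state that they are compared by the time-point tests.

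This needs no new data and runs in the same software. It costs a little more analysis work and an assumption that readings are missing at random. The article reports that the investigators are still blinded, so the change can be made and dated before the groups are revealed.
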